### 3. STUDY DESIGN

This study is an open label, dose escalation intervention trial with an adaptive design.

Volunteers will be exposed to predefined doses of cercariae in groups of three and subsequently seven volunteers. Dose escalation will be performed according to the schedule depicted in figure 1. If all three volunteers in one group show detectable circulating anodic antigen in serum, seven additional volunteers will be exposed to the same dose. If not all volunteers in one dose group become infected, the next group of three volunteers will be exposed to a higher dose. The highest dose is 60 cercariae. If one or more volunteers from group A of 60 cercariae have a positive CAA test, another seven volunteers will also be exposed to this dose (group B). If both group A and group B volunteers (total 10) were exposed to the same dose, the study will stop.

[figure not shown]

Figure 1. Dose schedule. In case all volunteers become positive for *Schistosoma* circulating anodic antigen, the additional volunteers will be exposed to the same cercariae dose (green arrows, continue from group A to B). In case not all volunteers become positive for *Schistosoma* circulating anodic antigen, the dose will escalate (red or yellow arrows).

In the clinical study performed earlier we exposed four groups to male cercariae. The starting dose for the first group (A1) was also 10 cercariae. After dose-escalation to 30 cercariae for the second group (A2), we decided to dose de-escalate and expose the third group (A3) to 20 cercariae because of the burden of severe adverse events related to acute schistosomiasis syndrome in one of the volunteers (please refer to paragraph 11.3 or the Product Dossier section 2.3.2: Human exposure" for more information). The last cohort was then also exposed to 20 cercariae (B). We have thus adjusted the dose escalation schedule to allow for slower escalation if needed.

In addition, we have included cercarial doses that are higher than those used in the male cercariae infection study. This has been done for two reasons: 1) rodent experiments suggest that female cercariae may be less likely to establish infection as worm counts rendered fewer numbers in single-sex female infected animals when compared to single sex male infected animals; and 2) because female worms do not fully mature if they are unable to mate, CAA levels are expected to be lower than in mixed or single-sex male infections.

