## 8. METHODS

### 8.1 Study parameters/endpoints

#### 8.1.1 Main study parameter/endpoint

- Frequency and severity of adverse events after controlled human *Schistosoma mansoni* infection with female cercariae
- The number of female cercariae at which 100% volunteers show detectable *Schistosoma mansoni* circulating anodic antigen

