### 8.7 Premature termination of the study

The study may be discontinued for one of the following reasons:

- a serious adverse event which is possibly, probably or definitely related to the infection with female *Schistosoma mansoni* cercariae;
- >50% of subjects in a dose group (more than 1 out of 3 from group A or more than 5 out of 10 from groups A and B) experience a grade 3 adverse event, possibly, probably or definitely related to infection with female *Schistosoma mansoni* cercariae and persisting at grade 3 for >48 hours during the 20 weeks follow-up;
- on advice from the SMC;
- on advice from the investigator, pending discussion with the SMC;
- on advice from the accredited METC.

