### 9.5 Safety committee

For this study, a safety monitoring committee (SMC) will be appointed which will be independent of the investigators and sponsor and has no conflict of interest with the sponsor of the study. This SMC will consist of three experienced clinicians qualified to evaluate safety data from clinical studies with schistosome infections. Their main responsibility will be assessing safety reports or serious adverse events and advising the sponsor/investigator on trial continuation. Dose will be escalated 10 weeks after infection, i.e. 2 weeks after treatment, of a dose group, whereby <100% of volunteers were infected (showed detectable serum CAA). This can be a group of 3 or a group of 10 volunteers. The SMC can advise the sponsor of the trial not to escalate the dose, stop the trial, withdraw individual subjects or suspend further study procedures. Should the sponsor decide not to fully implement the advice of the SMC, the sponsor will send the advice to the reviewing METC, including a note to substantiate why (part of) the advice of the SMC will not be followed.

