#### 10.1.2 Attack rate per dose group

The attack rate will be calculated by division of the number of volunteers with female *Sm* infection by the total number of volunteers in the per protocol analysis, multiplied by 100% (e.g. POS/TOTAL subjects \* 100%). Volunteers withdrawing from the trial procedures at any time after infection and before the end of the study, will be tabulated as positive and included in the per protocol analysis if they had a serum CAA  $\geq 1$  pg/mL at any timepoint after exposure and before praziquantel treatment. They will be excluded from the analysis if there was no positive serum CAA sample until the moment of withdrawal.

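### Below 60 cercariae, if group A is 3/3 positive but groups A and B together are not 10/10, section 3 stops the study and section 9.5 escalates the dose

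*Protocol*

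**What the plan says.** Protocol section 3 sets the sequence. Below the top dose, group B opens only after a full response in group A: "If all three volunteers in one group show detectable circulating anodic antigen in serum, seven additional volunteers will be exposed to the same dose". At the top dose the bar is lower: "If one or more volunteers from group A of 60 cercariae have a positive CAA test", seven more are exposed at 60 cercariae. The section then gives its end rule: "If both group A and group B volunteers (total 10) were exposed to the same dose, the study will stop". That rule mentions neither the infection result nor a particular dose.

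Section 9.5 gives an escalation rule: "Dose will be escalated 10 weeks after infection, i.e. 2 weeks after treatment, of a dose group, whereby <100% of volunteers were infected". It then names the sizes of group to which this applies: "This can be a group of 3 or a group of 10 volunteers".

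Two other places bear on the reading. Section 8.7 applies the term to ten people as well as three: "dose group (more than 1 out of 3 from group A or more than 5 out of 10 from groups A and B". Section 8.1.1 has as a main endpoint: "The number of female cercariae at which 100% volunteers show detectable" antigen. Section 4.4 states the aim as a 100% attack rate in 10 subjects.

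**The concern.** The two rules give opposite instructions for one outcome that the design can readily produce: three of three positive in group A, then at least one negative among the seven in group B, at a dose below 60. Section 3 ends the study there. Section 9.5 sends the next volunteers to a higher dose.

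The choice fixes the final dose, the number of healthy volunteers exposed, and whether the endpoint in section 8.1.1 can have a value. If the study ends at 9/10, no dose has met the 100% criterion. If it goes on, further people who gain no benefit are exposed to more cercariae, and section 13.1 says the earlier male-cercariae study suggested that acute schistosomiasis syndrome is dose-dependent. As written, the rule would be picked after the group B results are known.

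**Working it through.** The protocol gives no figure for this branch, so there is none to reproduce. The check traces the rules and then asks how often the disputed branch would occur.

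**Rule trace**

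| Outcome | Section 3 | Section 9.5 |
|---|---|---|
| Below 60, group A fewer than 3/3 | Escalate | Escalate |
| Below 60, A 3/3 and B 7/7 | Stop | Not triggered |
| Below 60, A 3/3 and B fewer than 7/7 | Stop | Escalate |
| At 60, A and B both exposed | Stop | No higher dose exists |

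Only the third row conflicts. It is also the only case that the group of ten in section 9.5 can describe: escalation from ten is possible only below 60, and below 60 ten volunteers exist only after 3/3 in group A.

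**Probability of the branch at one dose below 60**

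Let p be the true attack rate at that dose, with independent outcomes between volunteers. For female cercariae p is unknown, so every value here is an assumption. The value 0.82 is the attack rate that section 1 reports for 20 male cercariae and is illustrative only.

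- Group A fails: 1 − p³
- Conflict: p³(1 − p⁷)
- All ten positive: p¹⁰
- Conflict once group B is opened: 1 − p⁷

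For p = 0.80: p³ = 0.512 and p⁷ = 0.210, so group A fails with probability 0.488, the conflict arises with 0.512 × 0.790 = 0.405, and 10/10 occurs with 0.107.

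| p | Group A fails | Conflict | 10/10 | Conflict given A 3/3 |
|---|---|---|---|---|
| 0.70 | 0.657 | 0.315 | 0.028 | 0.918 |
| 0.80 | 0.488 | 0.405 | 0.107 | 0.790 |
| 0.82 | 0.449 | 0.414 | 0.137 | 0.751 |
| 0.90 | 0.271 | 0.380 | 0.349 | 0.522 |
| 0.95 | 0.143 | 0.259 | 0.599 | 0.302 |

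The conflict probability is greatest where 3p² = 10p⁹, that is p⁷ = 0.3 and p = 0.842, where it equals 0.418. It is the likeliest of the three outcomes only for p from about 0.835 to 0.906. Below that range, group A failure is likeliest; above it, 10/10 is.

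**Maximum number of volunteers, before replacements**

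Let k be the number of dose levels. Only Figure 1 gives it and I could not see that figure, so k is assumed.

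- Section 3: three at each of k − 1 doses and ten at the last, 3(k − 1) + 10 = 3k + 7.
- Section 9.5: ten at every dose, 10k.
- Difference: 7(k − 1).

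This gives 16 against 30 for k = 3, 19 against 40 for k = 4, and 22 against 50 for k = 5.

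**The case against.** The strongest case is that one sentence is loose and the rest agrees. The stop sentence directly follows the statements about 60 cercariae, so it can be read as the end rule for the top dose. The escalation sentence in section 3 and the Figure 1 caption both speak of not all volunteers becoming positive, without limiting this to group A, and could cover ten. A 10/10 result at a lower dose would need no stop rule, because nothing would then trigger escalation and the aim in section 4.4 would be met. Figure 1 may also draw an arrow from group B to the next dose.

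This shows which rule may have been intended, but it does not remove the conflict. The stop sentence refers to the same dose for both groups, not to the 60-cercariae dose just named. If the other sentences in section 3 do cover ten, that section contradicts itself as well as 9.5. A figure could only side with one of two contradictory statements. The safety committee may advise against escalation, but that is a safety override and does not set the default.

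Three points of the opposing case stand:

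- The attack rate is still reported at the final dose. Section 10.1.2 says: "The attack rate will be calculated by division of the number of volunteers with female" infection by the per-protocol total. The primary objective of safety, tolerability and attack rate is therefore still addressed if the study stops early.
- Doses are capped at 60, each volunteer is exposed once, and the committee reviews safety data before escalation.
- The volunteer maxima are worst cases. Reaching 10k needs the conflict branch at every dose below 60. Even at the peak of 0.418 each time, that is at most 0.418² = 17% for k = 3, 0.418³ = 7% for k = 4 and 0.418⁴ = 3% for k = 5.

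**Conclusion.** The point holds and must be fixed before any group B is exposed. It is a contradiction between two operative rules, not a detail left for later. It is confined to doses below 60 with 3/3 in group A and fewer than 10/10 overall; the rules agree in every other branch. Under independence and an assumed p between 0.70 and 0.95, the branch is a realistic outcome at any one dose and, once group B is opened, more likely than not across most of that range. What is unsettled is whether the study ends there or goes on to a higher dose, and so whether the 100% endpoint can still be reached. Safety oversight and reporting of the attack rate are not in doubt.

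**What to change.** State one rule in section 3 and refer to it from section 9.5. Either version works.

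- **(a) Stop after ten at one dose, whatever the result.** Delete the group of ten from section 9.5. Add to section 8.1.1 that if fewer than 10/10 are positive, no dose met the 100% target and the attack rate at that dose is reported with its exact 95% confidence interval (for 9/10, 55.5% to 99.7%). This changes sections 3, 8.1.1 and 9.5 and adds no volunteers.
- **(b) Stop only after 10/10 infected, or after groups A and B at 60 cercariae.** Keep the section 9.5 rule, and state the resulting maximum of ten volunteers per dose level before replacements. This changes sections 3 and 4.4. Relative to (a), the maximum rises by seven volunteers for each dose level below 60.

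Option (b) fits the stated aim of 10/10; option (a) keeps exposure lower. Either is a wording amendment only.

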## 4. STUDY POPULATION

### 4.1 Population (base)

Healthy subjects, male or female, aged 18-45 years old will be included in the study from the general population.

### 4.2 Inclusion criteria

In order to be eligible to participate in this study, a subject must meet all of the following criteria:

1. Subject is aged  $\geq 18$  and  $\leq 45$  years and in good health.
2. Subject has adequate understanding of the procedures of the study and agrees to abide strictly thereby.
3. Subject is able to communicate well with the investigator, is available to attend all study visits.
4. Subject will remain within Europe (excluding Corsica) during the study period and is reachable by mobile telephone from week 3 to week 8 of the study period.
5. Subject agrees to refrain from blood donation to Sanquin or for other purposes throughout the study period.
6. For female subjects: subject agrees to use adequate contraception and not to breastfeed for the duration of study.
7. Subject has signed informed consent.

### 4.3 Exclusion criteria

A potential subject who meets any of the following criteria will be excluded from participation in this study:

1. Any history, or evidence at screening, of clinically significant symptoms, physical signs or abnormal laboratory values suggestive of systemic conditions, such as cardiovascular, pulmonary, renal, hepatic, neurological, dermatological, endocrine, malignant, haematological, infectious, immune-deficient, psychiatric and other disorders, which could compromise the health of the volunteer during the study or interfere with the interpretation of the study results. These include, but are not limited to, any of the following:
  - body weight  $<50$  kg or Body Mass Index (BMI)  $<18.0$  or  $>30.0$  kg/m^2 at screening;
  - positive HIV, HBV or HCV screening tests;
  - the use of immune modifying drugs within three months prior to study onset (inhaled and topical corticosteroids and oral anti-histamines exempted) or expected use of such during the study period;
  - history of malignancy of any organ system (other than localized basal cell carcinoma of the skin), treated or untreated, within the past 5 years;
  - any history of treatment for severe psychiatric disease by a psychiatrist in the past year;

- history of drug or alcohol abuse interfering with normal social function in the period of one year prior to study onset.
- 2. The chronic use of any drug known to interact with praziquantel, artesunate or lumefantrine metabolism (e.g. phenytoin, carbamazepine, phenobarbital, primidone, dexamethasone, rifampicine, cimetidine, flecainide, metoprolol, imipramine, amitriptyline, clomipramine, class IA and III anti-arrhythmics, antipsychotics, antidepressants, macrolides, fluorchinolones, imidazole- and triazole antimycotics, antihistamines) Because lumefantrine may cause extension of QT-time, chronic use of drugs with effect on QT interval are excluded from the study.
- 3. For female subjects: positive urine pregnancy test at screening.
- 4. Any history of schistosomiasis or treatment for schistosomiasis.
- 5. Positive serology for schistosomiasis or elevated serum CAA at screening.
- 6. Known hypersensitivity to or contra-indications (including co-medication) for use of praziquantel, artesunate or lumefantrine.
- 7. Being an employee or student of the department of parasitology or infectious diseases of the LUMC.

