### 5.3 Escape medication

The trial physician may decide to abrogate the study for individual subjects according to the criteria described in section 8.4. Because early treatment of schistosomiasis infection has been shown to aggravate clinical symptoms in reported cases, the advantages and disadvantages of such escape medication should be carefully weighed. Escape medication should, in symptomatic cases, be accompanied by symptomatic treatment with corticosteroids.

Escape medication to abrogate the study for individual volunteers before week 8 of the study will be artemether/lumefantrine in a standard 6-dose treatment regimen over 3 days. Volunteers with early abrogation of infection are also treated with praziquantel 60 mg/kg at week 8.

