### 3. Possibility to abrogate infection

Artemisinin derivatives are a good alternative option for the treatment of *Schistosoma mansoni*, and may be useful in the early phase of infection, as it is also active on immature stages. This drug may thus be used to abrogate early infections in case of withdrawal of study discontinuation. Artemether/lumefantrine will be given in an oral loading dose of 4 mg/kg, followed by 2 mg/kg for 3 consecutive days (same treatment regime as for malaria). Because artemether is not available as single drug in the Netherlands, it can only be supplied as a combination drug with lumefantrine (artemether/lumefantrine, AL). The most common side effects of artemether/lumefantrine are headache, dizziness, coughing, myalgia or arthralgia and gastrointestinal side effects. For a complete description of side effects, please refer to the “bijsluiter” (see SPC artemether/lumefantrine).

In summary, volunteers of the trial have a substantial risk of discomfort. However, side effects can be managed both symptomatically and with directed treatment at any time during the study.

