#### h. Interaction with other products

The primary drug for treatment of *Schistosoma mansoni* infections, praziquantel is metabolized through cytochrome P450, CYP3A4. Any inducers or inhibitors of this enzyme can thus interfere with the efficacy of praziquantel. Use of these drugs is an exclusion criterium for participation in the study.

Because praziquantel only acts on mature schistosomes, artemisinin derivatives may be used to abrogate early infections. In the Netherlands artemether/lumefantrine (AL) is the only available oral drug with an artemisinin derivative. Because lumefantrine may cause extension of QT-time, chronic use of drugs with effect on QT interval are excluded from the study. AL is metabolized through CYP3A4, but may affect drug levels in CYP2D6 metabolism. Chronic use of this drug is thus also excluded.

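### Exclusion criteria 2 and 6 name artesunate, which the trial never uses, instead of artemether, a component of the planned escape drug

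*Protocol*

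**What the plan says.** Two exclusion criteria in section 4.3 concern the drugs a volunteer may need. Criterion 2 excludes "The chronic use of any drug known to interact with praziquantel, artesunate or lumefantrine metabolism", followed by a list of examples and a separate exclusion for chronic use of drugs that affect the QT interval. Criterion 6 excludes "Known hypersensitivity to or contra-indications (including co-medication) for use of praziquantel, artesunate or lumefantrine".

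The escape drug is set elsewhere. Section 5.3 states that infection abrogated before week 8 is treated with "artemether/lumefantrine in a standard 6-dose treatment regimen over 3 days", followed by praziquantel at week 8. Section 11.3, under the possibility to abrogate infection, names the same combination and describes it as given "in an oral loading dose of 4 mg/kg, followed by 2 mg/kg for 3 consecutive days (same treatment regime as for malaria"). It explains the choice of a combination product: "Because artemether is not available as single drug in the Netherlands". Section 13.1h agrees: "In the Netherlands artemether/lumefantrine (AL) is the only available oral drug with an artemisinin derivative".

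**The concern.** Criterion 6 is the check that a healthy volunteer, who gains nothing from taking part, can safely receive the drug used to end an early infection. Praziquantel acts only on mature worms (sections 11.3, 13.1h and 13.1j), so artemether/lumefantrine is the only antiparasitic option the protocol specifies before week 8. The criterion names one component of that product correctly and the other incorrectly. Read literally, it screens for a drug that will not be given and is silent on one that may be.

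The escape course is also described in two ways. A physician who consults section 11.3 instead of section 5.3 finds a weight-based schedule that cannot be matched directly to the one in the treatment section. The stake is clarity of safety text in an operative eligibility rule and a rescue instruction.

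**Working it through.** No stated figure needs reproducing. The check is a comparison of the places that name the drug or its regimen.

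**Drug name**

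| Place | Artesunate | Artemether |
|---|---|---|
| 4.3, criteria 2 and 6 | 2 | 0 |
| 5.3 | 0 | 1 |
| 11.3, possibility to abrogate infection | 0 | 5 |
| 13.1h | 0 | 1 |
| Total in the text available | 2 | 1 + 5 + 1 = 7 |

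Artesunate appears only in the two criteria. It cannot be read as a second planned option, because section 13.1h says artemether/lumefantrine is the only oral artemisinin product available in the country. Both criteria pair it with lumefantrine, the partner of artemether in the planned product, so they were evidently meant to cover that product.

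**What the literal text still catches**

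1. Criterion 6: a known reaction or contra-indication to lumefantrine, including one through co-medication, excludes the volunteer. As artemether is supplied only with lumefantrine, most known problems with the combination are caught this way. What is left is a known hypersensitivity or contra-indication specific to artemether.
2. Criterion 2: interactions with lumefantrine and QT-affecting drugs are covered. Section 13.1h, having named CYP3A4 as the enzyme that metabolises praziquantel, adds "Any inducers or inhibitors of this enzyme can thus interfere with the efficacy of praziquantel. Use of these drugs is an exclusion criterium". It then says "AL is metabolized through CYP3A4, but may affect drug levels in CYP2D6 metabolism". The CYP3A4 route is therefore excluded through praziquantel already, and little is left uncovered.

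**Regimen wording**

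| | Section 5.3 | Section 11.3 |
|---|---|---|
| Number of doses | 6 | not stated |
| Duration | 3 days | loading dose, then 3 consecutive days |
| Amount | not stated | 4 mg/kg, then 2 mg/kg |
| Frequency | not stated | not stated |
| Substance the mg/kg refers to | not applicable | not stated |

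The two descriptions share no quantity that can be set directly against the other except the 3 days, and section 11.3 does not say whether the loading dose falls within them. Counting the administrations in section 11.3 requires an assumed frequency. Some assumptions agree with section 5.3 and others do not. A difference in mg cannot be computed, because section 5.3 gives no amount.

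**The case against.** The strongest reply is that the slip has almost no practical effect. Lumefantrine is named in both criteria, artemether is never supplied without it, and a screening physician may well take artesunate to stand for the artemisinin class, since other parts of the protocol speak simply of artemisinin derivatives. Criterion 1 excludes conditions that could compromise the volunteer's health, eligibility is checked again on the day of exposure, and section 5.3 asks for escape treatment to be weighed carefully. All of this stands and limits the size of the point. It does not make the text correct: section 12.2 has monitors verify adherence to the criteria in full, and they should name the drug that may be given.

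On the regimen, section 11.3 equates its schedule with the one used for malaria and section 5.3 calls its course standard, so one regimen was probably intended and loosely paraphrased. That is fair. A reader might infer that the protocol contains two conflicting doses, or that one of them is wrong. The documents do not support this: at least one reading of section 11.3 agrees with section 5.3, and the SPC needed to settle it is not part of the protocol text.

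**Conclusion.** Wrong as written, and minor. Criteria 2 and 6 name a drug the protocol never plans to use and omit a component of the one it does. That rests on the text alone and is certain for the pages available. The consequence is small: under criterion 6 only a known problem specific to artemether escapes the literal wording, and under criterion 2 the remaining gap is slight.

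A reader might infer that volunteers known to be intolerant of the escape drug could generally be enrolled. The text does not support that, because lumefantrine is named in both criteria. Nor does the protocol show how often escape treatment would be used.

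The regimen mismatch holds as a wording point only. Endpoints, sample size and dose escalation are unaffected.

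**What to change.** Replace artesunate with artemether in exclusion criteria 2 and 6. Confirm the escape regimen against the artemether/lumefantrine SPC that section 11.3 already refers to, write the confirmed dose and timing into section 5.3 as the single operative instruction, and replace the mg/kg sentence in section 11.3 with a cross-reference to section 5.3.

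The cost is one word in each of two criteria, one check against the SPC, and one sentence in each of sections 5.3 and 11.3. No analysis or design element changes.
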